#### Planned Analyses

Proposed outcome analyses are summarized in Table 2.

For each of the main outcome measures, it is anticipated that regression analysis will be undertaken. The main factor of interest (group allocation) and confounding variables (eg, age, gender, ethnicity) will be entered into univariable regression analyses to determine the level of significance and to limit the number of variables entered into the multivariable analysis. Any factors with *P*≤.10 will be considered for inclusion in the multivariable analysis. Factors with *P*<.05 in the multivariable analysis will be considered as having a significant effect on toothbrushing time or gingival bleeding. Secondary outcomes will be explored in a similar manner.

If necessary, an intention to treat analysis will be performed; all enrolled and randomized patients will be included in the analysis and analyzed in the groups to which they were randomized.

**Table 2 table2:** A summary of proposed statistics for outcome analysis.

Outcomes	Method of analysis
Toothbrushing duration	Comparison of the 3 groups using an ANOVA, followed by 2-sample *t* tests (A vs B, B vs C, and A vs C) if any statistical significance is found
Bleeding score	Chi-square test
Plaque scores	Comparison of the 3 groups using an ANOVA, followed by 2-sample *t* tests (A vs B, B vs C, and A vs C) if any statistical significance is found
Number of breakages	Kruskal-Wallis test, followed by Mann-Whitney test (A vs B, B vs C, and A vs C) if any statistical significance is found
Number of missed appointments	Kruskal-Wallis test, followed by Mann-Whitney test (A vs B, B vs C, and A vs C) if any statistical significance is found
Total number of appointments	Kruskal-Wallis test, followed by Mann-Whitney test (A vs B, B vs C, and A vs C) if any statistical significance is found
Treatment duration	Comparison of the 3 groups using an ANOVA, followed by 2-sample *t* tests (A vs B, B vs C, and A vs C) if any statistical significance is found
Enamel demineralization	Chi-square test
App subjective quality	Comparison of the 3 groups and different section of the uMARS form by using the Kruskal-Wallis test.
App engagement	Comparison of the 3 groups using an ANOVA, followed by 2-sample *t* tests (A vs B, B vs C, and A vs C) if any statistical significance is found

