#### Data Collection

A complete data set will be collected at baseline, 3 months into treatment, 12 months into treatment, and at the end of treatment when the orthodontic appliances have been removed.

Two primary outcome measures have been selected, a health behavior outcome and a clinical outcome, as both are felt to be important. The outcome measures are timed toothbrush use and gingival bleeding scores (these scores indicate the amount of bleeding from the gums, where bleeding is an indicator of inadequate toothbrushing).

The secondary outcomes of interest are as follows: plaque scores, which indicate the amount of plaque on the teeth, where retention of plaque is an indicator of inadequate toothbrushing; number of fixed appliance breakages; number of missed and rescheduled appointments; treatment duration, number of appointments (including emergency appointments for appliance breakages); enamel demineralization (early tooth decay) on the upper anterior six teeth (using standardized photographs), as demineralization is a further indicator of inadequate toothbrushing and nonadherence to the appropriate diet; subjective quality of the app (sections E and F of the uMARS questionnaire); and app engagement.

The following baseline measurements and details will be obtained prior to treatment commencing: age, gender, malocclusion (type of dental bite), whether or not extractions (removal of teeth) are required for treatment, clinical photographs of the teeth (these will be compared with completion of treatment photographs to assess for enamel demineralization), bleeding score, and plaque score.

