#### Sample Size

The following assumptions have been made in the sample size calculation:

Data are normally distributed and initial comparison of the 3 groups would use an analysis of variance (ANOVA), followed by 2-sample *t* tests for A versus B, B versus C, and A versus C if any statistical significance is found.

The significance level is *P*<.05 with 80% power.

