##### Timed Toothbrush Use

Using a clinically relevant difference of 20 seconds between groups and a SD of 23.6 seconds from a paper by Tesini and Perlman [21] (standardized difference=0.85) and accounting for multiple testing, 29 patients are required in each group (n=87). Assuming a dropout of 20%, the sample size is 35 per group.

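### Each primary outcome has two unranked analyses, the Table 2 test and a multivariable regression, and the protocol does not say which one decides

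*Protocol article*

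**What the plan says.** Data Collection (Phase 2) states: "Two primary outcome measures have been selected, a health behavior outcome and a clinical outcome". These are timed toothbrush use and gingival bleeding. Three places then bear on how they are tested.

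- **Sample Size** assumes, for both outcomes, that "initial comparison of the 3 groups would use an analysis of variance (ANOVA"), with pairwise t tests to follow if it is significant. It adds: "The significance level is *P*<.05 with 80% power".
- **Planned Analyses, Table 2** gives brushing duration "Comparison of the 3 groups using an ANOVA, followed by 2-sample" t tests. It gives the bleeding score a chi-square test.
- **Planned Analyses, text** says: "For each of the main outcome measures, it is anticipated that regression analysis will be undertaken". Group allocation and confounders such as age, gender and ethnicity enter univariable regressions. Those with P≤.10 are considered for the multivariable model. Factors with P<.05 "in the multivariable analysis will be considered as having a significant effect on toothbrushing time or gingival bleeding".

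The text presents Table 2 as the summary of the outcome analyses, yet the regression paragraph carries its own rule for declaring significance on the same two outcomes. Neither analysis is called primary, supporting or sensitivity.

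**The concern.** A trial should have one analysis per primary outcome whose result is the verdict. Here an unadjusted test and an adjusted model both address the same group effect, and the plan gives no rule for the case where one is significant and the other is not. The hints conflict: the sample size basis suggests that Table 2 leads, while the only sentence that declares an effect on the two primary outcomes belongs to the regression.

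Two things are at stake. If success can be claimed on either analysis, the false-positive rate for that outcome exceeds its nominal level. And a reader of the results cannot tell whether the reported analysis was the planned one. Fixing the covariate set would not cure this, because two tests of one hypothesis would remain.

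**Working it through.** **1. Which analysis was the trial sized on?** Inputs from Sample Size: power 80%; brushing 20 s with SD 23.6 s (standardized difference given as 0.85), 29 per group; bleeding 15 points with SD 20 (0.75), 38 per group; an allowance for multiple testing whose divisor is not stated. The two-sample normal approximation, taken as two-sided, is n = 2(z₁₋α/₂ + z₀.₈₀)²/d².

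- At α = 0.05/3: 2 × (2.394 + 0.842)² = 20.94. Bleeding: 20.94/0.75² = 37.2, so 38, as stated. Brushing: 20.94/0.85² = 28.98, so 29, as stated (30 with the unrounded ratio 20/23.6).
- At α = 0.05: 28 for bleeding and 22 for brushing, neither as stated.

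So the sizing fits pairwise t tests at 0.05/3. That level is an inference from the figures. The regression rule is a flat P<.05 with no such adjustment.

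**2. The analyses side by side**

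| | Brushing time | Bleeding score |
|---|---|---|
| Sample Size | ANOVA, then t tests | ANOVA, then t tests |
| Table 2 | ANOVA, then t tests | Chi-square |
| Planned Analyses text | Multivariable regression, P<.05 | Multivariable regression, P<.05 |

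Brushing has two candidates. Bleeding has two in Planned Analyses, and the one listed in Table 2 is not the one it was sized on.

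**3. Size of the effect if either may decide.** Two independent tests at 0.05 would give 1 − 0.95² = 9.75%, which serves as a reference ceiling. These tests share the same data and are strongly correlated, so the rate was simulated.

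Setting: three arms of 37 (46 × 0.8 = 36.8); global test of group at 0.05 in each analysis; one normal covariate. Following the written rule, both group and covariate must pass the P≤.10 screen before the regression can declare an effect. Assumptions not in the protocol: covariate R² of 5-30%, and a median split to make the bleeding percentage fit a chi-square test.

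| | Brushing: ANOVA or regression | Bleeding: chi-square or regression |
|---|---|---|
| No effect: either significant | about 5.7-6.1% | about 7-7.5% |
| A-C d = 0.75, B midway: verdicts differ | about 4-7% | about 27-29% |

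A separate simulation with four covariates, 38 or 46 per arm, R² from 0 to 0.50 and group screened gave about 5-6% for brushing and 6-8% for bleeding. With 8,000 runs the Monte Carlo standard error at 6% is √(0.06 × 0.94/8,000) = 0.27 points, so differences of a few tenths carry no meaning.

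**4. What drives the bleeding disagreement.** Under the same alternative, global power was about 82% for ANOVA and about 61% for the chi-square test on the median split. Most of the 27-29% is therefore the chi-square test missing effects that an analysis of the continuous score finds. It measures dichotomization more than the lack of ranking.

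**The case against.** The strongest reply is that the plan follows a common sequence: unadjusted group comparisons in Table 2, then an adjusted model that decides for the main outcomes. Table 2 states no significance level and no success rule; a significant result there only opens the pairwise tests. The article's wording is provisional, and ranking analyses is often left to a statistical analysis plan, which is not shown. This reading is reasonable but the document does not secure it. Sample Size rests on the Table 2 approach for brushing, and the article itself publishes the regression's rule for significance. That is a stated conflict and goes beyond omitted detail.

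A reader might infer more than the documents support, in three ways.

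- *That both analyses run throughout at the full 5%.* This is not established: the stated sample sizes fit 0.05/3 for the pairwise t tests.
- *That the error rate for brushing reaches 7-8%.* Rates of 6.0-7.9% arise only if group is always kept in the regression. As written, group allocation goes through the same P≤.10 screen as the confounders, which removes most of the excess.
- *That the 80% power is lost for brushing if regression is used.* With group kept in the model, simulated regression power was 83-94% against about 82% for ANOVA.

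It is also fair that naming either analysis would remove the ambiguity. The choice of regression below is a recommendation, with its reason given there.

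**Conclusion.** The concern stands as an unresolved conflict in Planned Analyses: two unranked analyses per primary outcome, one of them with its own significance rule, and a sample size that points to the other approach. The inflation is modest: about 5.7-6.1% in place of 5% for brushing, and about 7-7.5% for bleeding. For brushing the two verdicts would differ in about 4-7% of trials under the alternative examined. These figures rest on an assumed covariate R² of 5-30%, an assumed median split for bleeding, and the literal reading that group itself is screened.

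The 27-29% disagreement for bleeding should not be cited as the cost of failing to rank the analyses. It depends on a split that appears nowhere in the protocol and mostly reflects the chi-square test's loss of power, a separate defect. The change is worth making because it is cheap and settles which result is the trial's answer, not because the error rate is seriously out of control.

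**What to change.** In Planned Analyses, name one deciding analysis for each primary outcome: a linear regression of the continuous score (seconds of brushing; percentage of bleeding surfaces), with randomized group always in the model and exempt from the P≤.10 screen, and with pre-specified covariates. Read the pairwise contrasts from that model: C versus A, and the comparisons with B that Recruitment (Phase 2) calls important. Test them at the multiplicity-adjusted level used in the sample size, and state that level. In Table 2, label the brushing and bleeding tests as unadjusted supporting analyses that do not determine significance. Regression is preferred because it keeps both outcomes continuous, as the sample size assumes, and in the simulations its power was no lower than that of ANOVA.

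Cost: the screening paragraph and two rows of Table 2 are reworded. No extra data or patients are needed. The article reports that nobody had yet been recruited; in any case the change should be dated before the planned review of 3-month data from the first 15 participants per group.

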##### Gingival Bleeding

An estimated clinically relevant difference of 15% and a SD of 20% (standardized difference=0.75) was used, based on advice from [name] (clinical trials coordinator, Restorative Dental Sciences, UCL Eastman Dental Institute, Faculty of Medical Sciences, UCL), who has experience in commercial trials using these outcome measures. The same assumptions were followed as described above, and this indicated a sample size of 38 per group. With the 20% dropout factored in, the sample size calculation is 46 per group (n=138).

Therefore, 138 patients will be recruited. There are a number of assumptions in these calculations; therefore, an internal pilot will be conducted, and the calculations will be repeated using 3-month data for the first 15 patients recruited to each group.

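### The regression plan puts the randomized group through the same univariable P≤.10 screen as the covariates, names no baseline score as a covariate, and does not say whether it or Table 2 is primary

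*Protocol article*

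**What the plan says.** All references are to Phase 2 of the protocol article.

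- **Planned Analyses, text.** "The main factor of interest (group allocation) and confounding variables (eg, age, gender, ethnicity) will be entered into univariable regression analyses". One stated purpose is "to limit the number of variables entered into the multivariable analysis". Factors with P≤.10 are considered for the multivariable model, and P<.05 in that model is read as a significant effect on brushing time or bleeding. Secondary outcomes follow the same route. No exemption is made for group, and no covariate is fixed in advance.
- **Planned Analyses, Table 2.** Brushing time and plaque: "Comparison of the 3 groups using an ANOVA", then pairwise t tests. Bleeding: a chi-square test. None of these is adjusted. Neither Table 2 nor the regression is called primary.
- **Data Collection.** The list of baseline details ends with "bleeding score, and plaque score", and Table 1 places both at visit 1. The list contains no baseline brushing time and no ethnicity, although ethnicity is one of the example covariates.
- **Sample Size.** "The significance level is *P*<.05 with 80% power". For bleeding: "An estimated clinically relevant difference of 15% and a SD of 20% (standardized difference=0.75) was used". For brushing: "Using a clinically relevant difference of 20 seconds between groups and a SD of 23.6 seconds".

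**The concern.** Group is the factor the trial exists to estimate, so it belongs in every model. Under the rule as written, the adjusted effect is estimated only when the unadjusted one has already reached P≤.10. A comparison that baseline adjustment would have made clear can therefore be lost.

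Covariates chosen by their observed P values make the model, and with it the adjusted estimate, depend on the data. The usual standard error takes no account of that choice. Randomization makes such a screen unnecessary: differences between arms at baseline are due to chance, and covariates earn their place by predicting the outcome.

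A baseline measurement of the same score is the natural candidate covariate for bleeding and plaque, and it is already collected. With two analyses of the same outcome and no ranking between them, either could be presented as the result.

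**Working it through.** **1. The plan's own sample size.** Use n per group = 2(z₁₋α/₂ + z₀.₈)² / d², with two-sided α = 0.05/3 for three pairwise comparisons. The article says multiple testing was accounted for but not how; this α fits. Then 2 × (2.394 + 0.842)² = 20.94.

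- Bleeding, d = 15/20 = 0.75: 20.94/0.5625 = 37.2, so 38 as stated.
- Brushing, d = 0.85 as rounded in the article: 20.94/0.7225 = 28.98, so 29 as stated. Unrounded, d = 20/23.6 gives 30.

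The sample size reproduces and is not affected by this point.

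**2. How often group is screened out.** Take 38 per group, means of 0, d/2 and d, and the overall 3-group F test of group. The noncentrality is λ = n × 2 × (d/2)².

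- d = 0.75: λ = 38 × 2 × 0.1406 = 10.69. The chance that P exceeds .10 is 10.0%.
- d = 0.5: λ = 38 × 2 × 0.0625 = 4.75. The chance is 40.0%.
- No effect: 90%, by definition of the threshold.

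With 37 per group (46 recruited less 20% is 36.8), the first two become 10.7% and 41.1%.

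**3. Power of the overall test at P<.05.** Baseline adjustment with correlation ρ turns λ into λ/(1−ρ²). The screened route was simulated with 38 per group and 3,000 trials per setting. Baseline bleeding and three unrelated covariates were offered to the screen, and group was kept only if its own P was ≤.10. The article gives no ρ, so 0.3 to 0.7 is an assumed range.

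| Effect | ρ | Unadjusted | Pre-specified, baseline-adjusted | Screened |
|---|---|---|---|---|
| 15 points (0.75 SD) | 0.3 | 82.8% | 86.2% | 83.7% |
| | 0.5 | 82.8% | 92.0% | 87.6% |
| | 0.7 | 82.0% | 98.3% | 89.0% |
| 10 points (0.5 SD) | 0.3 | 46.5% | 50.4% | 47.1% |
| | 0.5 | 48.5% | 60.6% | 52.6% |
| | 0.7 | 47.4% | 77.4% | 55.2% |

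As a check, the noncentral F distribution at 0.75 SD gives 83.1% unadjusted, and 86.6%, 92.6% and 98.7% adjusted. Repeat simulations moved the screened figures by one to two points.

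**4. Type I error.** With no true effect and 6,000 trials, the screened route rejects in 4.3%, 3.4% and 3.0% of trials at ρ = 0.3, 0.5 and 0.7. The pre-specified model rejects in about 5%.

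**5. What baseline adjustment gives pairwise.** The required n is multiplied by 1−ρ². From 37.2 this gives 33.9, 27.9 and 19.0, so 34, 28 or 19 per group. Pairwise power at 38 per group rises from 80.9% to 84.9%, 91.6% or 98.6%.

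**The case against.** Several stronger readings are tempting, and the article does not support them.

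- **That baseline scores are excluded from adjustment.** The covariates are introduced as examples, and factors passing the screen are only considered. The scores are unnamed, not ruled out, and a full list is often left to the analysis plan. What stands is that any baseline score added would face the same screen.
- **That Table 2 compares bleeding by ANOVA and t tests.** It assigns bleeding a chi-square test. Among the scores with a baseline value, the ANOVA wording applies only to plaque, a secondary outcome.
- **That the treatment comparison could vanish.** The Table 2 tests and the univariable regression report group in every case. Only the adjusted estimate can be lost.
- **That the screen produces false positives.** Step 4 shows no inflation; the procedure is conservative.
- **That the trial becomes underpowered.** At the planned effect, screened power in step 3 stays above the 80% target and is no worse than the unadjusted test. The 40% figure belongs to an effect two-thirds of the planned one.

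The size of the gain is also uncertain. Baseline is taken before braces are fitted and follow-up during or after treatment. The Introduction cites plaque levels 2 to 3 times higher with fixed appliances, so a high correlation cannot be presumed. At the planned effect with 37 per group, the loss from screening was only 0.2 points at ρ = 0.2 and 2.9 points at ρ = 0.4.

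None of this removes the main point. The threshold, its purpose and the decision rule are stated in the article, and they apply to group.

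**Conclusion.** The point holds in this form. The article states a selection rule that lets the randomized group drop out of the adjusted model, and that picks covariates by their P values. It names no baseline score as a covariate, and it leaves two analyses of each primary outcome unranked.

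At the planned bleeding effect, the cost against a pre-specified baseline-adjusted model is roughly 1 to 3 points of power at ρ = 0.3, 4 to 5 at 0.5 and 9 to 10 at 0.7. It is larger if the true effect is smaller: at 0.5 SD about 3, 8 and 22 points. False-positive risk is not raised.

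These sizes rest on assumed correlations, normally distributed scores, a middle group lying halfway between the other two, and group being screened as one three-level factor. The existence of the defect rests on none of these. The absence of ethnicity from the baseline list is minor and may come from condensing the full protocol.

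**What to change.** - Delete the P≤.10 screen.
- For each primary outcome, name one pre-specified linear model as the primary analysis, always containing group and a short covariate list fixed in advance.
- For bleeding, include the baseline bleeding score and let this model replace the chi-square test. For plaque, include the baseline plaque score. Brushing time has no baseline value, so its model carries group and the fixed list only.
- Take the A-B, B-C and A-C contrasts from that model, and label the unadjusted tests in Table 2 as supportive.
- Use ethnicity only if it is added to the baseline data.

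The cost is wording. Apart from ethnicity, nothing new has to be collected, and the sample size need not rise. The article reports that no patients had been recruited, so on that footing the change could be made before any outcome data exist.

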##### Gingival (Gum) Bleeding

A periodontal probe (specialized probe to test gum health) will be used; the presence of bleeding within 10 to 30 seconds of probing is indicative of inflammation of the gingivae (gums). Scores will be recorded for all teeth anterior to the molars (incisors, canines, and premolars) and will be recorded as the percentage of the total number of tooth surfaces (6 surfaces per tooth). A binary score will be assigned to each surface (1 for bleeding present, 0 for no bleeding).

A calibration exercise will be conducted prior to commencing the study. The key factors affecting consistency of probing technique are probe position and pressure applied (ideally 20 to 25 grams). The bleeding assessment technique will therefore be reviewed and observed in a volunteer subject by a gold standard examiner following training performed on models. It is not possible to do duplicate bleeding assessments as the act of repeated probing can cause bleeding; therefore, it is essential that this aspect of the study is well controlled for.

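### Bleeding and plaque are scored at four visits, but the tests named take one value per patient and cannot include anyone who lacks the analysed score

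*Protocol article*

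**What the plan says.** On timing, Data Collection (Phase 2) states: "A complete data set will be collected at baseline, 3 months into treatment, 12 months into treatment, and at the end of treatment". Table 1 ticks bleeding and plaque at all four visits. Each visit yields one percentage per patient; the bleeding score "will be recorded as the percentage of the total number of tooth surfaces (6 surfaces per tooth").

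On analysis, Table 2 in Planned Analyses gives the bleeding score a "Chi-square test". Plaque gets "Comparison of the 3 groups using an ANOVA, followed by 2-sample *t* tests (A vs B, B vs C, and A vs C") if the first test is significant. The text above the table also anticipates a regression for the main outcomes, with group and confounders for which age, gender and ethnicity are the examples. Neither baseline score nor visit is mentioned.

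On who is analysed, intention to treat is to be done only where it proves necessary. In that case, "all enrolled and randomized patients will be included in the analysis and analyzed in the groups to which they were randomized".

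On numbers, Sample Size assumes: "Data are normally distributed and initial comparison of the 3 groups would use an analysis of variance (ANOVA"), followed by t tests. For bleeding: "The same assumptions were followed as described above, and this indicated a sample size of 38 per group", and then "With the 20% dropout factored in, the sample size calculation is 46 per group (n=138").

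**The concern.** A chi-square test on patients, an ANOVA, a t test, or a regression with group and patient characteristics takes one outcome per patient. A patient not seen at the analysed visit has no such outcome and cannot enter without a further step, which the article does not describe. A chi-square test on pooled tooth surfaces would change nothing here, because an unseen patient contributes no surfaces.

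Two things are at stake. Scores already collected from patients who later miss a visit contribute nothing to the comparison. And if loss is related to earlier bleeding, comparing only those who attend removes more high scorers from the worse arm and understates the difference between A and C. Follow-up is long: the Introduction gives an average treatment time of 2-3 years and cites one study in which 43% did not complete treatment. Loss at the later visits is therefore a practical matter.

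**Working it through.** **1. Reproduce the plan's figure.** Inputs from Sample Size: difference 15, SD 20, power 80%, significance level 0.05, multiple testing allowed for. The method of adjustment and the sidedness are not stated; I assume two-sided tests with 0.05/3 for three pairwise comparisons.

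n = 2 × (z₁ + z₂)² × (SD/difference)² = 2 × (2.394 + 0.842)² × (20/15)² ≈ 37.2, so **38 per group**, as stated. Without adjustment the result is 28, which does not match. The figure is thus a calculation with one value per patient.

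**2. How many would enter.** 38 × 1.2 = 45.6, rounded up to 46, as stated. With 20% lost, 46 × 0.8 = 36.8 per group, or 138 × 0.8 ≈ 110 of 138 in total. Pairwise power (normal approximation) is 79.5% at 36.8 per group, against 88.5% if all 46 had a value.

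**3. Loss unrelated to bleeding.** Suppose a fraction m lacks the analysed visit, an earlier score is available for everyone, and r is the correlation between the two scores. A likelihood-based model multiplies the variance of the attenders-only comparison by 1 − m·r². The documents give no r, so I take 0.3 to 0.7, with m = 0.2.

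| r | variance factor | fall in standard error | equivalent n per group |
|---|---|---|---|
| 0.3 | 1 − 0.2 × 0.09 = 0.982 | 0.9% | 36.8/0.982 = 37.5 |
| 0.5 | 1 − 0.2 × 0.25 = 0.950 | 2.5% | 36.8/0.950 = 38.7 |
| 0.7 | 1 − 0.2 × 0.49 = 0.902 | 5.0% | 36.8/0.902 = 40.8 |

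Simulations under unrelated 20% loss agree, at about 1% to 6%. Any gain from the baseline covariate itself is not counted, because a single-visit analysis could also adjust for baseline.

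**4. Loss that depends on earlier bleeding.** Illustrative simulation, 4,000 trials per setting: 46 per arm, SD 20, control mean 40, true A-C difference 15 at every post-baseline visit, equal correlation r between visits. The log-odds of loss after the 3-month visit are −1.386 + 0.06 × (3-month score − 40), giving 19-20% lost on average. The comparison is of mean scores at the last visit, not of the chi-square test in Table 2. The standard deviation of each estimate is in brackets.

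| r | attenders only | using earlier scores | 15 minus attenders only |
|---|---|---|---|
| 0.3 | 14.45 (4.53) | 15.05 (4.60) | 0.55 |
| 0.5 | 14.03 (4.57) | 15.07 (4.61) | 0.97 |
| 0.7 | 13.64 (4.47) | 15.02 (4.48) | 1.36 |

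With heavier loss (28-34% in A, 17-18% in C) and r of 0.5 to 0.7, the attenders-only difference averaged 12.8 to 14.0, a shortfall of 1.0 to 2.2 points. Here the model removes bias but does not improve precision.

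**5. Scale.** The standard error of the attenders-only difference at 37 per arm is 20 × √(2/37) = 4.65. A shortfall of 0.55 to 2.2 points is about 0.12 to 0.47 of that.

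**The case against.** Inflating for dropout while planning intention to treat is ordinary practice. The inflation protects power; intention to treat says which group a patient belongs to. Any of the named tests could include every randomized patient after imputation, and an article may leave imputation to the full protocol or analysis plan. This stands. A reader might infer that the plan contradicts itself outright, but the documents do not support that: the all-randomized sentence is conditional, and a document not shown could reconcile it.

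Three other strong readings also fail. A reader might infer from Sample Size that bleeding will be tested by ANOVA and t tests; Table 2 says chi-square, though the consequence for a patient without a score is the same. A reader might infer that the other visits are discarded by design; no section names the visit to be tested, so non-use follows from the form of the tests and is not a stated rule. And a reader might take it that patients with poor hygiene are the ones lost. Nothing in the article shows this, and the Abstract says there are no useful predictors of noncompletion. That statement concerns completing treatment, so it does not show that loss is neutral either.

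It is also fair to say that the form of the regression is left open, that the effect is small, and that a mixed model still omits a patient with no post-baseline score. What remains is that Table 2 fixes specific tests for outcomes measured four times, and those tests neither use the repeated scores nor, by themselves, deliver the population described beneath them.

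**Conclusion.** The point holds as a mismatch between the tests named, the visits scheduled and the population described. It is worth correcting, but its effect is modest. If loss depends on earlier bleeding, an attenders-only comparison would understate a 15-point difference by about 0.5 to 2 points, which is under half a standard error. If loss is unrelated to bleeding, the cost is a standard error about 1-6% larger than necessary. Both ranges rest on assumed correlations of 0.3 to 0.7, and the first also on assumed loss models. They apply to a visit after 3 months; the gain would differ if 3 months were the analysed visit. The documents do not establish that the trial's result will be biased.

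**What to change.** In Planned Analyses, for bleeding and plaque:

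- Replace the Table 2 entries by a linear mixed model for repeated measures on the post-baseline visits, with group, visit, group-by-visit interaction and baseline score as covariate.
- Report the A vs C contrast at one named fixed-time visit (3 or 12 months). Treat end of treatment with care: its timing differs between patients, and treatment duration is itself an outcome.
- Make intention to treat unconditional. State that every randomized patient with at least one post-baseline score enters in the assigned group, and that patients with none are counted and reported by group.
- Add one sensitivity analysis that assigns worse scores to patients lost.

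The cost is a change of wording and some extra analysis work, with no new visits or patients. The model relies on loss being explained by the observed scores, which the sensitivity analysis is there to probe. The article reports that nobody had been recruited, so on its account the change could be made before any data existed.
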